***Assessment Timeline:*** Assessments will be completed at study enrollment and thereafter at monthly intervals up to 3 months corrected age, then at 3-months corrected age, 6-months corrected age, 9-months corrected age, 12-months corrected age, 18-months corrected age (optional), and 24-months corrected age (optional). The number of assessments prior to 3 months corrected age will vary by preterm status and age of enrollment. Optional assessments will be completed if (i) the study is still ongoing and (ii) the caregiver agrees to do so. If infants are unable to complete any required assessment sessions, an attempt to re-schedule will be made. If infants are unable to complete a testing session, their participation in the study will not be affected; however, the study team will appropriately document the missing data.

***Additional monitoring:*** Intervention therapists and study team members will monitor infant response to intervention sessions, caregiver engagement (caregiver- and therapist-report) compliance to key principles, percentage of intervention sessions completed, the dosage of Activity Playbook activities achieved (caregiver report), any adverse events/changes in medical status, additional services received outside of study participation, general medical and health updates, and additional information if relevant for study purposes. Surveys or medical chart reviews may be utilized to capture the above information throughout study participation.

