***Standard of Care Group:***

Participants will receive services as assigned by their clinical team. Families will receive information on early intervention services, including speech therapy, occupational therapy, and/or physical therapy. The child will be referred by the clinical team, if eligible, and the family is interested in these services. Participants will not be prevented from receiving any service that they would otherwise be eligible for as a result of participation in this study. Study staff will monitor the frequency and type of additional services received.

For all participants, we will monitor access to recommended services and follow up if families report having difficulty accessing desired services and would like assistance. We will provide all participants with contact information for study staff.

*Assessment Timelin****e:*** Assessments will be completed at study enrollment and thereafter at monthly intervals up to 3 months corrected age, then at 3-months corrected age, 6-months corrected age, 9-months corrected age, 12-months corrected age, 18-months corrected age (optional), and 24-months corrected age (optional). The number of assessments prior to 3 months corrected age will vary by preterm status and age of enrollment. Optional assessments will be completed if (i) the study is still ongoing and (ii) the caregiver agrees to do so. If infants are unable to complete an assessment session, we will attempt to reschedule the appointment. If the infant does not complete an assessment session, their participation in the study will not be impacted; however, the study team will appropriately document the missing data.

*Additional monitoring:* Study team members will monitor for any adverse events/changes in infant medical status, general medical and health updates, and therapy services received outside of study participation. Additional information may be collected, if relevant for study purposes. Surveys or medical chart reviews may be utilized to capture the above information throughout study participation.

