*Documentation*: Primary data entry and storage will be completed through the SRAlab REDCap system. Paper surveys and forms will subsequently be added to REDCap by a member of the study team. Intervention forms/surveys may include, but not be limited to: a home environment checklist, demographics, subjective caregiver survey, visit summary, caregiver identified goals, PRIME-SP, PRIME-P (completed monthly by the caregiver(s)), adverse event log, documentation of dosage of caregiver-provided activities from Activity Book and documentation of any additional services received. (See supporting documents for details). Some intervention sessions and assessment sessions will be videoed for training purposes and fidelity checks. Adverse events will be documented and reported to the PI, IRB, and Sponsor, according to IRB guidelines.

*Minimization of risk*: This is a minimal risk study that involves provision of a physical therapy intervention and has no increased risk compared to other standard physical therapy interventions. Several strategies will also be implemented to minimize any potential risk to participants.

- Therapists will adhere to institutional vaccination policies and will self-screen before each intervention or assessment session.
- Intervention therapists and applicable study staff will complete a multi-day training on protocol guidelines and recommendations.
- Medical stability of infant and family readiness to approach will be evaluated prior to beginning the consent process.
- Collaborative communication with caregivers and/or allied health staff and/or medical chart reviews to monitor for any medical status changes or procedure updates within the NICU.
- Tolerance to therapy or assessment procedures will be monitored. If child experiences physiologic or behavioral responses or instability, the therapist will modify the procedures or end the session.
- Any unanticipated adverse event that results in discontinuation of the session will be documented.
- Infant response during intervention sessions will be monitored by the therapist and/or caregiver, and activities will be modified based on infant tolerance.
- Data will be maintained in a secure data capture system, with access limited to those identified as members of the study team.

*Audio/Video Recording*: Video and audio recordings will be used to evaluate the fidelity of intervention delivery and characterize standard of care therapy sessions.

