# Risks to Participants

This is a non-invasive, minimal risk study that does not involve collection of specimens. Potential risks and associated prevention or amelioration strategies are listed below.

Risk of harm due to intervention or assessment procedures

There is no significant increase in risks associated with participation in intervention sessions compared to standard physical therapy sessions. Some potential risks include:

For infants who are intubated, there is small risk of unplanned extubation. This will be minimized by the presence of the study nurse who will monitor the infants position and stability during the therapy sessions. For infants with respiratory or nutritional support (e.g., nasal cannula, NG, or G-tubes) there is a small risk of pulling the tube out of position or site irritation/bleeding during the intervention, standard of care therapy, or assessments. Care will be taken in handling of the infant at all times, and any indication of physiological changes that do not self-resolve or any additional concerns will be immediately reported to the study team and/or medical assistance will be requested, as appropriate. All study staff will be appropriately trained, and experienced at working with infants.

If a child has surgery, the intervention will be paused and surgical team clearance will be obtained, as appropriate before resuming study activities. If a child undergoes a procedure to remove a G-tube, study therapists will follow-up with the surgical team and modify the intervention or assessments based on their guidance. All surgical interventions will be documented.

Additional risks to participation include infant skin irritation, fatigue, or frustration. Intervention and assessment sessions will be completed according to infant tolerance. Changes in behavior state or stress cues will result in modification of the therapy session, as needed. Any loss of balance/falls with upright activities (e.g. stepping) will not be considered adverse events, as they are developmentally appropriate.

All assessments are standard infant outcome measures and as such have no known risks to the infant.

Risk of infant distress while wearing sensors

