As the data coordinating center, SRAlab will be responsible for monitoring data fidelity, and will generate reports on a regular basis that will be shared with participating sites and reviewed at PI meetings to ensure data accuracy and completeness. SRAlab will also monitor adverse events and ensure all reporting requirements are met across sites. Meetings between PIs will be convened to address problems with study recruitment, and intervention implementation, and adverse events.

Interim results will be communicated with each site at PI meetings. Decisions on continuing of stopping the study will be made at each scheduled meeting or at additional meetings convened as necessary to address study findings or adverse events.

Data will be stored on REDCap indefinitely, and de-identified data as well as data analysis results will be provided to each site and made available to other investigators with necessary safeguards to ensure privacy of participants.

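### The protocol excludes every fall in upright activities from adverse events and makes no exception for a fall that injures the infant

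*Protocol*

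**What the plan says.** Under Risks to Participants, in the part on harm from intervention or assessment procedures, the protocol states that any loss of balance or fall in upright activities, with stepping as the example, "will not be considered adverse events, as they are developmentally appropriate". Slightly earlier the same section provides that "any indication of physiological changes that do not self-resolve or any additional concerns will be immediately reported to the study team", or that medical help is sought.

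The duties that depend on an event being an adverse event are in Procedures Involved. The documentation paragraph lists an adverse event log among the study forms and says: "Adverse events will be documented and reported to the PI, IRB, and Sponsor, according to IRB guidelines". The list of measures to minimise risk adds: "Any unanticipated adverse event that results in discontinuation of the session will be documented". The multi-site research section says that "SRAlab will also monitor adverse events and ensure all reporting requirements are met across sites".

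Medical status is followed in both arms. In the intervention arm the additional monitoring covers "any adverse events/changes in medical status, additional services received outside of study participation". For the standard of care arm the text reads: "Study team members will monitor for any adverse events/changes in infant medical status, general medical and health updates". Therapists also record the outcome of each NICU and home session in REDCap, and at home each session opens with a caregiver survey.

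**The concern.** The exclusion is broader than its justification. Infants learning to stand and step fall often, and logging every harmless tumble would fill the adverse event log with noise. That argument does not extend to a fall during a study procedure that injures the infant. The sentence nevertheless draws no line by consequence.

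Adverse event data carry weight in this trial. The section on monitoring participant safety says that no DSMB is required. The multi-site section places decisions on continuing or stopping in investigator meetings, which consider study findings and adverse events. The protocol also claims that the intervention carries no more risk than ordinary physical therapy. If injurious falls in study sessions can properly be left off the log, the record used to test that claim is incomplete in a way nobody reading the log could see.

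**Working it through.** No calculation decides the point. It turns on whether any other provision brings an injurious fall back into the adverse event count.

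1. **Reach of the rule.** The sentence opens with the word *any* and classifies by activity (upright, with stepping as the example), not by consequence. No exception appears for injury, medical attention or early end of a session, there or in any other section.

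2. **The stated reason.** Developmental appropriateness describes the fall. It does not describe an injury that results, so the rule is wider than the reason offered for it.

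3. **Other provisions, side by side.**

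| Provision | What triggers it | Does it bring an injurious fall into the count? |
|---|---|---|
| Documentation when a session is ended (Procedures Involved) | An adverse event that is unanticipated and ends the session | Not clearly: the fall has been declared not to be an adverse event, and calling it developmentally appropriate makes it expected |
| Reporting to the PI, IRB and sponsor (Procedures Involved) | An adverse event | Not for the fall itself, which has been taken out of that class |
| Cross-site oversight (multi-site research) | An adverse event | Same |
| Reporting of concerns (Risks to Participants) | Physiological change that does not resolve, or any other concern | Reaches the study team or medical help; nothing says it is logged as an adverse event |
| Medical-status monitoring, both arms | A change in medical status | May reveal the injury; nothing says it is then counted or linked to the session |
| Session records and caregiver survey (Procedures Involved) | Every session | May record what happened; no step leads from there to the adverse event log |

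The first three provisions depend on the classification that the exclusion removes. The last three may bring the injury to light but do not say how it is classified.

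4. **Where an under-count would fall.** The rule names no arm and follows text about both intervention and assessment sessions. Study exposure differs, however. Inputs: sessions up to twice a week until 12 months corrected age (Procedures Involved); Block C from 3 to 12 months; assessments at 3, 6, 9 and 12 months in both arms.

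- Length of Block C: 9/12 × 52 = 39 weeks.
- Therapy sessions in Block C at full attendance: 39 × 2 = 78 per intervention infant.
- Scheduled study contacts over this period: 78 + 4 = 82 per intervention infant, against 4 per standard of care infant.

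These are maxima for contact, not counts of upright practice, which will occupy only part of the later sessions. They show the direction of any imbalance.

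5. **Size.** The number of missed events would be sessions with upright activity × fall rate × injury rate per fall. The protocol supplies none of the three, so the size cannot be calculated.

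**The case against.** The strongest reply is that the sentence excludes the fall and does not mention injuries. A fracture or head injury is a different event from the fall that caused it, and can be entered as an adverse event in its own right or as a change in medical status. This stands in part. A reader might infer that the protocol rules injuries out, or that injuries from falls can never be counted. The text says neither, and several routes could bring such an injury to notice. What remains is that nothing instructs staff to classify it as an adverse event, and a therapist following the sentence literally has a written reason not to.

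Second, a reader might take the exclusion to operate only against the intervention arm. It does not. Assessments in both arms include standing, through the AIMS and the sensor recordings. Only the difference in exposure stands.

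Third, a reader might suppose that the harms most specific to the therapy are the ones removed. The documents do not show this. Unplanned extubation, tube displacement, site bleeding, skin irritation and fatigue are named as risks and none is excluded.

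Fourth, the detailed rules for the adverse event log may be in supporting documents that the protocol cites and that are not shown. That may be so, but the protocol's own sentence is unqualified and would still need to agree with them.

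Finally, no adverse event endpoint is defined, and neither the primary outcome nor any stated hypothesis is affected. That is correct; the point concerns safety recording only.

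**Conclusion.** The point holds as a defect in the definition. The protocol fixes a categorical exclusion, does not say how a fall with injury is handled, and ties its documentation and reporting duties to the class from which falls have been removed. Sites could reasonably apply this in different ways, and any under-count would fall mainly in the intervention arm because of its greater study exposure.

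The size is unknown. A reader might multiply 2 × 52 × 110 = 11,440 sessions and treat this as the scale of the problem. The documents do not support that use. It assumes full attendance, although 110 per arm is the figure planned with 30% attrition; it includes the early months, when stepping is not in question; and it contains no fall or injury rate. It describes contact, not harm.

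The conclusion rests on reading the sentence as written and on no other section supplying an exception. If the supporting documents for the adverse event log already code injuries from falls as adverse events, what remains is a wording conflict to remove.

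**What to change.** In Risks to Participants, limit the exclusion to falls without injury. Add that a fall in a study session or assessment, in either arm, that leads to injury, medical contact or early end of the session is recorded as an adverse event. Reconcile this with three places: the session-ending rule in Procedures Involved, so that the word *unanticipated* does not let such a fall drop out again; the general reporting sentence in the same section; and the monitoring paragraphs for the two arms, so that an injury found through medical-status follow-up is entered on the log in the same way.

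The cost is about one sentence, matching edits elsewhere and one item on the existing adverse event log. The downside is a few more adverse event reports. Harmless falls stay excluded, and neither the therapy nor the assessments change.

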### Risk of loss confidentiality

To mitigate this risk, caregivers and infants will be assigned and identified by a unique study ID. The key that links caregiver or infant names with study ID will be password protected on a secure server housed in SRAlab or at the infant’s recruitment site, and accessed only by authorized, IRB-approved study personnel. All electronically stored data, emails, or participant records will be double password protected. Any paper copy documents will be stored in locked cabinets at the respective sites; documents containing identifiable information will be stored separately from study data. All data will be analyzed and presented in aggregate form, with no identifying information attached that would reveal a participant’s identity.

Note: The only exception to participant confidentiality is that we are legally obligated to report evidence of child abuse or neglect. We will not ask caregivers about child abuse or neglect, but if caregivers tell us about child abuse or neglect we are required by law to report their name to state authorities. In addition, should caregivers report thoughts and plans of harming themselves or others, with imminent risk to their baby or someone else, we may take additional steps to ensure the safety of the caregiver, baby, and/or others. We will also ask caregivers if they would like to be with us when we contact the proper authorities.

# Potential Benefits to participants

We cannot guarantee any benefit to participation in the study or proposed intervention. However, infants in the intervention group may benefit from the high-dose, individualized therapy based on scientific evidence and clinical practice. Based on caregiver responses to the monthly parent subjective form, we will attempt to facilitate access recommended services outside of the study for all participants.

# Data Management and Confidentiality

***Data Analysis Plan***

### Power Analysis:

The motor subscale score of the Bayley-4 at 12-months corrected age is the primary outcome measure. It is a standardized score with a range of 45-155, a mean of 100, and a standard deviation (SD)=15. For this study, we will consider a significant effect of the intervention to be a Bayley motor score that is 8 points (~0.5 SD) higher in the intervention group than in the control group at 12-months corrected age. Assuming similar variability in this clinical trial with SD=15, a sample size of n=77 subjects per arm will provide 90.1% power with two-sided α=0.05 significance level to detect an 8-point difference in Bayley-4 motor scores at 12 months based on a two-sample equal-variance t-test. This would correspond, for example, to an improvement from the average 12-month Bayley-4 Motor score of 87.7 among patients (n = 77) recently assessed in our Early Childhood Clinic to an average score of 95.7. If we conservatively assume larger SD=17.5 due to possibly higher variability in Bayley-4 Motor scores in this high-risk population, we would still have sufficient 79.4% power to detect an 8-point difference between treatment arms. Assuming 30% attrition, up to 220 patients (110 per arm) will be required in order to obtain 154 patients evaluable for primary outcome. Assuming 20% attrition, up to 192 patients (96 per arm) will be required in order to obtain 154 patients evaluable for primary outcome. Power calculations were done using PASS 2020 software.

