# Study Endpoints:

*Primary Study Endpoints:*

- Completion of the 12-month assessment time-point for up to 240 infants, across all sites.
- Analysis of the Bayley-4 motor scores at the 12-month testing time-point for up to 240 infants, across all sites.

*Secondary Study Endpoints:*

- Evaluation of whether the intervention results in a reduction in the severity of motor delays, compared to the standard of care group, that can be detected as early as 3-months corrected age.
- Evaluation of the intervention’s impact on caregiver health-related quality of life.

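### The sample-size figures conflict: the power section supports at most 220 infants, other sections say 240, and the printed powers and the 192 do not match 77 per arm

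*Protocol*

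**What the plan says.** **Power Analysis.** The target effect is "a Bayley motor score that is 8 points (~0.5 SD) higher in the intervention group than in the control group". On power: "Assuming similar variability in this clinical trial with SD=15, a sample size of n=77 subjects per arm will provide 90.1% power", at "two-sided α=0.05 significance level to detect an 8-point difference in Bayley-4 motor scores at 12 months", "based on a two-sample equal-variance t-test". A second scenario begins "If we conservatively assume larger SD=17.5 due to possibly higher variability" and reports 79.4% power. Attrition is then added: "Assuming 30% attrition, up to 220 patients (110 per arm) will be required in order to obtain 154 patients evaluable for primary outcome". A parallel sentence gives 192 (96 per arm) at 20% attrition.

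**Elsewhere in the Protocol:**
- Study Summary: sample size 240, without qualification.
- Study Endpoints, first primary endpoint: "Completion of the 12-month assessment time-point for up to 240 infants, across all sites".
- Participant Population(s): a ceiling on consents of 180 (Lurie/Prentice) plus 60 (UIC), total 240. Beside it stands the number who complete or are needed to answer the question: 123 plus 31, total 154.
- Procedures Involved, Informed Consent and Randomization: an infant counts as enrolled once consent is complete, and randomisation comes afterwards.

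**The concern.** A reader who wants to know how many infants the trial will recruit finds 192, 220 and 240, and only the first two are derived. The largest cannot be reached from the stated inputs, because the worst attrition considered (30%) gives 220. The number 240 also changes meaning. It is the sample size in one place, a ceiling on consents in another, and in Study Endpoints a ceiling on infants who complete the 12-month visit, where the population table has 154.

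The power statement has a separate inconsistency: the printed percentages do not belong to the printed number per arm. At stake is whether the recruitment target, the loss assumption and the power can be read as one design. These are the figures against which recruitment and retention will later be judged.

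**Working it through.** **Inputs (Power Analysis):** difference 8; SD 15 or 17.5; two-sided α 0.05; two-sample equal-variance t-test; 77 per arm. Consent and completion counts come from Participant Population(s).

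**1. Power.** The noncentrality parameter is δ = 8 / (SD × √(2/n)), with 2n − 2 degrees of freedom. Power is the probability that the noncentral t exceeds the two-sided 5% critical value in either tail.

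| n per arm | SD | δ | critical t | power |
|---|---|---|---|---|
| 75 | 15 | 3.266 | 1.976 | 90.06% |
| 75 | 17.5 | 2.799 | 1.976 | 79.42% |
| 77 | 15 | 3.309 | 1.976 | 90.80% |
| 77 | 17.5 | 2.836 | 1.976 | 80.47% |

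The printed 90.1% and 79.4% are both reproduced to the decimal at 75 per arm. Of the sizes tried (73 to 78), no other reproduces both. A normal approximation at 77 per arm does not explain them either: it gives 91.1% and 81.0%. At 77 per arm the printed values are too low by 90.8 − 90.1 = 0.7 points and 80.5 − 79.4 = 1.1 points. All of these are fixed-sample powers.

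**2. Inflation for attrition.** N = evaluable / (1 − attrition).
- 30%: 154 / 0.70 = 220. This reproduces the plan's figure.
- 20%: 154 / 0.80 = 192.5, so 193, or 194 (97 per arm) with equal arms. The printed 192 leaves 192 × 0.80 = 153.6.

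**3. What 240 against 154 would mean.** Non-evaluable fraction if the ceiling is reached and only the stated number is evaluable:
- Overall: 1 − 154/240 = 35.8%
- Lurie/Prentice: 1 − 123/180 = 31.7%
- UIC: 1 − 31/60 = 48.3%

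All three exceed 30%. The columns also split the sites differently: 180:60 is 75:25, while 123:31 is about 80:20 (123/154 = 79.9%). One common loss rate therefore cannot connect them.

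**4. The opposite reading.** If 240 infants are enrolled and losses are 20–30%, 240 × 0.70 = 168 to 240 × 0.80 = 192 are evaluable. Power at SD 15 is then 93% (84 per arm) to 96% (96 per arm).

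**The case against.** The strongest reply is that 240 is a ceiling and 154 a requirement, and dividing a required minimum by a permitted maximum does not give an attrition rate. Both scenarios, 192 and 220, fit under 240. The Protocol also gives reasons why consented infants could outnumber evaluable ones without being lost to follow-up:
- Siblings from multiple births are randomised together, but only the one at highest risk is assessed (Randomization).
- The 6 to 10 pilot infants are analysed only if the protocol is not substantially changed (Study Aims).
- Consent precedes randomisation (Procedures Involved).

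The 180:60 ceilings are also close to the expected site accrual in Qualifications to Conduct Research: 35–40% of about 110 eligible infants a year is 38 to 44, against 13 at UIC.

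Most of this stands, and it rules out three stronger readings that a reader might infer.
- **That the trial plans for 36% loss, or 48% at UIC.** It does not say so. These are ratios that apply only if the ceiling is reached with 154 evaluable.
- **That 220 recruited would leave about 141 evaluable** (220 × 154/240), with power near 88% and 77%. This applies the ratio behind one number to a different number, a combination the Protocol never states.
- **That the open range lets an unblinded team choose when recruitment ends.** The multi-site section does send interim results to investigator meetings that decide on continuing or stopping. Nothing there makes the recruitment target depend on results.

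The reply does not remove the conflict. The Protocol offers none of these reasons as the basis for 240. The Study Summary gives 240 as the sample size, not as a ceiling. The 220 and 192 are themselves worded as upper limits. Headroom at consent also cannot explain attaching 240 to completers in Study Endpoints.

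**Conclusion.** The stated figures conflict and should be corrected; the design itself is not shown to be inadequate. All the sections are compatible with needing 154 evaluable infants, 77 per arm, and that number gives adequate fixed-sample power on the Protocol's own assumptions (8 points, SD 15 or 17.5, equal-variance t-test, two-sided 0.05).

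Three things are wrong as written:
- **Target.** 240 is 20 above the largest derived number, has no stated basis, and is used in Study Endpoints as if it could be the number of completers.
- **Power.** The percentages are those of 75 per arm. The error is 0.7 and 1.1 points and conservative, so it is editorial. That 75 was the size actually entered is an inference from the match.
- **Inflated size.** 192 should be 193, or 194 with equal arms: a difference of one or two infants.

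The target is the part that matters most, because it determines what counts as full recruitment and what loss the trial is built to withstand.

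**What to change.** 1. Use one randomisation target with one attrition rate in Study Summary, Study Endpoints, Participant Population(s) and Power Analysis, for example 220 at 30%.
2. Either label 240 as a ceiling on consents and say what the extra 20 cover (co-siblings, pilot infants, loss before randomisation), or keep 240 as the target and state the non-evaluable fraction it assumes (about 36%).
3. Make the site rows follow that choice. At 220 and 30%, rows of 176 and 44 leave 123.2 and 30.8, together 154. If UIC must reach 31 by itself, 31/0.70 = 44.3, so it needs 45.
4. Reword the first primary endpoint so that 240 is not the number completing the 12-month assessment. Make the same change to the companion endpoint on analysis of the scores.
5. Restate the fixed-sample power for 77 per arm as 90.8% (SD 15) and 80.5% (SD 17.5), or state 75 per arm if that was the calculation and carry it through the inflation.
6. If the 20% scenario is kept, change 192 (96 per arm) to 194 (97 per arm).

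The cost is a text amendment. No infants are needed beyond the existing ceiling of 240, and no procedure changes.
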